#### Viral clearance on or before d8 of treatment (outpatients)

This will be tabulated and examined using logistic regression incorporating terms for study arm and the minimisation factors used for randomisation, if the number of patients is sufficient.

#### Evaluate the relationship between post COVID19 health and psycho-social consequences and the clinical outcomes of the study

This will be defined prior to analysis, and may include combined analyses with other studies, such as the ISARIC study.

#### **7.1.5 Safety**

The worst toxicity grades (including AEs of special interest) experienced during active treatment will be compared between the study arms using the Mann-Whitney U test. P-values will be interpreted in the context of the multiple tests performed. This analysis will be restricted to events that occur in more than 10% of patients in either arm.

All Serious Adverse Events (including SARs and SUSARs) will be tabulated.

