| Pregnancy Test                                                      | X                              |                 |          |                 |          |          |          |          |                 |          |           |                        |                                    |                                     |
| PK testing                                                          |                                | X               |          | X               |          | X        |          |          | X               |          | X         |                        |                                    |                                     |
| COVID19 Health
and Wellbeing
Follow up
Survey
(Appendix 3)          |                                |                 |          |                 |          |          |          |          |                 |          |           | X                      | X                                  | X                                   |

1. Observations: Heart rate, temperature, oxygen saturations, blood pressure, respiratory rate
2. IMP should start to be administered within 24 hours of randomisation
3. Bloods/Nasopharyngeal swabs can be taken +/- 48 hours from scheduled time point unless otherwise specified. Screening bloods/NP swabs should be performed within 96 hours of randomisation
4. Nasopharyngeal swabs on day 1 should be taken as close to T0 (time of first drug administration) as possible
5. Patients discharged prior to day 15 should follow the outpatient schedule of assessments from point of discharge. Patients should return for clinic visit where possible, or be followed up by phone call if unable to attend

6. Follow-up visit at day 29 and 60 may be performed by telephone if patient is unable to attend clinic
7. Serum pregnancy test, for patients of child bearing potential only
8. Screening COVID-19 test can be done using any valid method of testing
9. PK Samples should be taken at the following times:

- Day 1: pre dose and 0.5 hours post dose
- Day 3: pre and 0.5 hours post dose
- Day 5: pre and 0.5 hours post dose
- Day 8: Pre dose
- Day 10: Pre dose

In addition, 16 volunteers (8 male, 8 female) will have more frequent sampling for PK on days 1 and 3 after either dose that day. Hours post dose: 0.5, 1, 2, 7, 12

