| COVID19 Health
and Wellbeing
Follow up
Survey
(Appendix 3)          |                             |                 |          |          |          |          |       |       |                |       |        | X      | X                                 | X                                 |

1. Observations: Heart rate, temperature, oxygen saturations, blood pressure, respiratory rate
2. IMP should start to be administered within 24 hours of randomisation

3. Bloods/Nasopharyngeal swabs can be taken +/- 48 hours from scheduled time point unless otherwise specified. Screening bloods should be performed within 96 hours of randomisation
4. Nasopharyngeal swabs on day 1 should be taken as close to T0 (time of first drug administration) as possible
5. Follow-up visit at day 15, 29 and may be performed by telephone if patient is unable to attend clinic
6. Serum pregnancy test, for patients of childbearing potential only. Result must be confirmed negative before IMP is released to patient.
7. Screening COVID-19 test can be done using any valid method of testing
8. AE, con med and WHO COVID Ordinal Severity Scale assessments should be made by phone call on days 1 – 10.
9. Optional nasopharyngeal swab may be done by patient at home if possible and safe to transport
10. To minimise the time spent in the clinic, patients can return home after screening and have IMP delivered to their home following randomisation
11. PK sampling should only be done where site have provision to take a predose sample (screening or day 1 pre-dose) AND a post dose sample (30 minutes after dosing), and have facilities to spin samples within 4 hours.

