|                                                                                                                                                               | WHO COVID 10 point ordinal severity scale level                                                                                                                                                             | Days 8, 29, 60                                 |
|                                                                                                                                                               | Overall survival                                                                                                                                                                                            | Up to and including day 60                     |
|                                                                                                                                                               | Inpatients only:
Viral clearance on or before d8 **                                                                                                                                               | Day 8                                          |
|                                                                                                                                                               | Inpatients only:
Duration of pyrexia in days (defined as a temperature $\geq 38^{\circ}\text{C}$ )                                                                                                | Up to and including day 60                     |
| Evaluate the safety and tolerability of favipiravir in the study population                                                                                   | Adverse events                                                                                                                                                                                              | Up to and including day 60                     |

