### **Day 1-10^1**

WHO COVID 10 point ordinal severity scale assessment (daily – worst value in last 24 hours)

Documentation of concomitant medications (daily)

Assessment of adverse events (daily)

Routine observations/vital signs\* (daily)

Routine clinical blood tests: days 1,3,8,11 (+/- 48 hours)

Blood tests for immunological and epigenetic testing: days 1, 3 (+/- 48 hours)

Symptom directed clinical examination if clinically indicated

Administration of IMP (if applicable)

Nasopharyngeal swab (for SARS-CoV-2 PCR assessment and Viral Load): days 1 (at time of first dose), 3, 8, 10, 13 (+/- 48 hours)

Pharmacokinetic samples: according to the sample schedule (Appendix 5)

 Patients discharged during this time should follow the outpatient trial schedule. The timing of the first dose of favipiravir should be documented as Time zero (T0). The nasopharyngeal swab should be taken as close to this time as possible.

 On day 8, two swabs should be taken – one to be sent for immediate COVID-19 testing by any valid method, the other to be stored for later analysis of viral load.

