### **Day 1-10^1**

Dispensing of IMP (patients on favipiravir arm)  
WHO COVID 10 point ordinal severity scale assessment (daily – worst value in last 24 hours)  
Documentation of concomitant medications (daily)  
Assessment of adverse events (daily)  
Nasopharyngeal swab (for SARS-CoV-2 PCR assessment and viral load): day 8  
Administration of IMP and completion of Patient Diary (patients on favipiravir arm)

 Assessments on day 1-10 will be performed by telephone

 IMP may be dispensed in clinic following randomisation where possible, or couriered to the patient's home

 NP swab may be performed at home by the patient provided this is safe to do and safe transport to research laboratory has been arranged.

 Baseline PK sample can be taken at screening or pre-dose day 1. PK sampling will only be undertaken where sites can accommodate both pre and post dose sampling, and have the facilities to spin samples within 4 hours.

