## COVID-19 Health and Wellbeing Follow up Survey (Appendix 3)

 Day 15 assessment should be done in clinic - if patient is unable to attend clinic, a follow-up telephone assessment should be done.

 Optional if patient unable to attend clinic

 Compliance check should be done at next follow-up visit if patient cannot attend on day 15

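### The toxicity comparison in 7.1.5 is limited to active treatment; read as the 10 dosing days, it includes no scheduled post-baseline laboratory value from patients managed wholly as outpatients

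*Protocol*

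**What the plan says.** Protocol 7.1.5 Safety describes the only formal between-arm safety test: "The worst toxicity grades (including AEs of special interest) experienced during active treatment will be compared between the study arms", using the Mann-Whitney U test. It adds a frequency filter: "This analysis will be restricted to events that occur in more than 10% of patients in either arm". SAEs are tabulated separately, without that window.

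Other sections bear on the window:

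- **Objective.** Table 1 has the objective "Evaluate the safety and tolerability of favipiravir in the study population", with adverse events up to and including day 60 as the endpoint.
- **Treatment length.** 5.10.1 sets favipiravir treatment at 10 days. The schedules ask for dosing to start within 24 hours of randomisation.
- **Outpatient bloods.** The outpatient schedule and 4.2.2 place routine bloods at screening and at days 15, 29 and 60. For the days between, "Assessments on day 1-10 will be performed by telephone". Note 3 of the schedule allows some tolerance: "Bloods/Nasopharyngeal swabs can be taken +/- 48 hours from scheduled time point unless otherwise specified". The day 15 bloods carry a further note: "Optional if patient unable to attend clinic".
- **Inpatient bloods.** The inpatient schedule has routine bloods on days 1, 3 and 8, then day 15. 4.2.1 also lists day 11. After discharge, "Patients discharged prior to day 15 should follow the outpatient schedule of assessments from point of discharge"; 4.2.1 says the same: "Patients discharged during this time should follow the outpatient trial schedule".
- **Known laboratory effects.** 5.7.2 lists uric-acid and ALT/AST rises among the common reactions. The background section on previous human use describes the uric-acid rises as asymptomatic. 6.1.4 makes ALT or AST above 3 x ULN an adverse event of special interest.

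**The concern.** Several of the drug's recognised effects are laboratory findings, and daily telephone calls cannot be expected to detect asymptomatic ones. WHO scores 2 and 3 are eligible, so patients treated at home are part of the target population. If the comparison covers only the dosing days, it leaves out bloods that the trial already schedules for these patients, and it covers much less time than the endpoint in Table 1.

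5.7.2 also notes that earlier studies used lower doses and shorter courses than this trial, which makes comparative laboratory data at this dose more useful. At stake is how well the formal safety comparison can show known laboratory effects. The primary efficacy result is not involved.

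**Working it through.** **Step 1. Schedule arithmetic.** The protocol gives no figure to reproduce here; the check is a count of draws.

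- Last dosing day: day 10, or about day 11 if the first dose comes 24 hours after randomisation.
- Earliest day 15 draw: 15 - 2 = day 13. Latest: 15 + 2 = day 17.
- Day 13 falls after day 11, so the draw is outside the dosing days even with a late start.

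Scheduled post-baseline routine draws that enter the comparison, for a patient never admitted:

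| Window | Draws counted |
|---|---|
| Days 1-10 (or to day 11) | 0 of 3 |
| Through the day 15 visit window (day 17) | 1 of 3, optional if the patient cannot attend |
| To day 60 | 3 of 3, each optional if the patient cannot attend |

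An inpatient who stays in hospital contributes at least days 3 and 8 under the first row. One discharged on day 5 has already had the day 3 draw and loses day 8.

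**Step 2. Interaction with the 10% filter.** This step is illustrative. The protocol gives neither the share f managed wholly as outpatients nor event rates. Assume f = 25% or 50%, a true rate of a laboratory event of 5% on control and 20%, 25% or 30% on favipiravir, and no in-window laboratory value from outpatients.

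- Patients per arm with in-window values: m = 151 x (1 - f), rounded: 151, 113 and 76 for f = 0, 25% and 50%.
- Events needed if all 151 are the denominator: smallest integer above 15.1, which is 16.
- Events needed if patients tested are the denominator: smallest integer above 11.3 = 12 (f = 25%), or above 7.6 = 8 (f = 50%).
- Probability of passing: 1 - (1 - qc)(1 - qt), where q is the binomial probability of at least the needed number of events among m patients in that arm.

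| f | Denominator | 5% v 20% | 5% v 25% | 5% v 30% |
|---|---|---|---|---|
| 0 | 151 | 0.999 | >0.999 | >0.999 |
| 25% | 151 | 0.957 | 0.998 | >0.999 |
| 25% | 113 tested | 0.997 | >0.999 | >0.999 |
| 50% | 151 | 0.454 | 0.822 | 0.970 |
| 50% | 76 tested | 0.991 | >0.999 | >0.999 |

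**Step 3. Visible difference.** For 5% v 20%, the difference over 151 per arm is 15.0 x m/151: 15.0 points at f = 0, 15.0 x 113/151 = 11.2 at f = 25%, and 15.0 x 76/151 = 7.5 at f = 50%.

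The filter therefore matters mainly when f is large and untested patients stay in the denominator. The planning table in 7.1 has 34% (control) and 51% (experimental) ambulatory at day 15. That is status after dosing and includes discharged inpatients, so it says little about f.

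**The case against.** **The term may be settled elsewhere, and another reading exists.** Analysis windows are often defined in the SAP, which is not shown. In 4.2.2 the outpatient end-of-treatment compliance check sits at the day 15 visit, and 5.6 collects concomitant therapy up to an end-of-treatment visit. Outpatients have no day 10 clinic visit. If the window closes at day 15, the day 15 bloods count. This stands as an alternative reading. However, 7.1.5 does not say so, 5.10.1 points to 10 days, and control patients, who take no study drug, are given no window at all. The protocol chose a restriction here, and its wording should be made to work.

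**The most important signal is covered.** ALT/AST above 3 x ULN is reported as an SAE up to day 60 (6.1.4) and tabulated (7.1.5). Other adverse events are recorded and appear in the final listings (6.1.2.2, section 10). Bloods taken because of symptoms still count. This stands and limits the point to the formal comparison.

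**An on-treatment comparison is legitimate.** Agreed, and it should be kept as a supportive analysis.

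**Stronger readings that a reader might infer.**

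- That discharged inpatients also contribute no laboratory values. They do not lose the draws taken before discharge.
- That the comparison is biased between arms. Both arms follow the same blood schedule, so the documents show under-detection and no more.
- That 6.1.2.2 makes day 29 the proper end of the window. That rule ends follow-up of unresolved events; it sets no limit on new ones, and the endpoint runs to day 60.

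**Conclusion.** The point holds, conditional on reading active treatment as the 10 dosing days, which is the natural reading. On it, patients managed wholly as outpatients contribute 0 of 3 scheduled post-baseline laboratory draws to the only formal between-arm toxicity comparison. If the window is meant to close at the day 15 visit, they contribute one, but the text would need to say so and to state a window for the control arm.

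The consequence is reduced sensitivity in both arms, mainly for uric acid and lower-grade laboratory changes. The count of draws rests on the protocol alone. The effect on the 10% filter rests on assumed outpatient shares and event rates: for 5% v 20% over all 151 per arm, the chance of passing is 96% at a 25% share and 45% at a 50% share, and it returns to 99% or more when patients tested are the denominator. This should be fixed, because bloods already planned are left out of the comparison and the remedy is cheap.

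**What to change.** In 7.1.5:

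1. Compare worst grade in both arms from randomisation through at least the day 15 visit window (day 17), and preferably over the whole adverse-event period to day 60 in Table 1.
2. Keep an on-treatment comparison as supportive, defined as days 1-10 in both arms.
3. Report ALT/AST above 3 x ULN and uric-acid elevation by arm whatever their frequency, with the number of patients tested as the denominator.

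The cost is wording and a few table rows, with no new visit, procedure or data. There are two downsides. The longer window adds some late COVID-related events in both arms, which the supportive comparison helps to separate. Day 15 bloods recover only abnormalities that persist after dosing.

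Separately, the clinical team should know that the laboratory-based removal criteria in 5.8 have no scheduled on-treatment value in outpatients. Whether to add a blood test is a clinical decision and not part of this change.

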**During these times, only randomisations sent by email will be processed.**

**Please check local site Pharmacy opening times – patients should be randomised no later than 1 hour before local site Pharmacy closes.**

**Out of hours randomisation availability is dependent on site Pharmacy and Nursing staff availability – this may differ between sites and at different times according to the progress of the pandemic. Sites will be kept informed of any changes to this service.**

When the patient has consented, a screening number should first be obtained by contacting the CRUK CTU, Glasgow.

When screening is complete and eligibility confirmed, the CRUK CTU Glasgow should be contacted again. The patient's eligibility criteria will be checked and, if eligible, a trial number and trial arm will be allocated at this point.

All patients must be registered/randomised onto the trial prior to commencement of trial treatment.

A minimisation algorithm incorporating a random component will be used to allocate patients to either experimental or control arm. The factors used in the minimisation will be:

- Site
- Age (16 - 50; 51 – 70; 71+)
- History of hypertension or currently obese (BMI>30 or obesity clinically evident) (yes; no)
- <7 days duration of symptoms (yes; no; unknown)
- Sex (male; female).
- WHO COVID ordinal severity score at baseline (2 or 3; 4)

With the patient's consent, their GP will be informed of their involvement in the trial.

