### **6.1.2.2 Recording of Adverse Events**

Full details of AEs including the nature of the event, including the event term, start and stop dates, severity, seriousness and causality (relationship of the AE to each trial IMP) and outcome will be recorded in the patient's medical records. All AEs must be reported from the start of treatment and followed until:

- They resolve
- If present at pre-treatment, until the AE returns to the level observed at that time
- The AE is confirmed as unlikely to ever resolve

If none of the criteria above are met by follow-up day 29, the AE no longer requires to be followed up. Perceived lack of efficacy is not an AE.

An exacerbation of a pre-existing condition is an AE.

The Investigator does not need to actively monitor patients for AEs once the trial has ended, unless required.

Adverse events occurring in the period between consent and randomisation do not require to be recorded in the CRF if they are unrelated to any study specific screening procedure.

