## 7 STATISTICS AND DATA ANALYSIS

### 7.1 Trial Design and Sample Size

The study is designed as an open-label randomised (1:1) phase II/III study which allows for early stopping for lack of efficacy or clear superiority in the experimental arm.

The study is powered to detect an improvement corresponding to an odds ratio of 1.95 in the cumulative odds of the WHO COVID 10-point ordinal severity scale assessed at day 15. This is equivalent to the probability of a patient having a better outcome at this time if allocated to experimental as compared to control of 66% (50% under null hypothesis). The following table illustrates that improvement:-

|                              | WHO COVID 10-point ordinal severity scale                                                                                | Assumed percentages on control arm at day 15* | Percentages on experimental arm at day 15 with odds ratio=1.95 |
|------------------------------|--------------------------------------------------------------------------------------------------------------------------|-----------------------------------------------|----------------------------------------------------------------|
| Death                        | Death                                                                                                                    | 11%                                           | 6.0%                                                           |
| Hospitalized; severe disease | Mechanical ventilation pO 2 /FIO 2 <150 and vasopressors, dialysis or ECMO                         | 5%                                            | 2.9%                                                           |
|                              | Mechanical ventilation pO 2 /FIO 2 >150 ( SpO 2 /FIO 2 >200) or vasopressors | 7%                                            | 4.4%                                                           |

|                            |  |                                                                                      |     |       |
|----------------------------|--|--------------------------------------------------------------------------------------|-----|-------|
|                            |  | ICU - intubation & mechanical ventilation, $pO_2/FIO_2 > 150$ or $SpO_2/FIO_2 > 200$ | 5%  | 3.3%  |

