### 7.1.2 Primary Efficacy Analysis

The primary analysis will use cumulative odds ordinal regression with proportional odds. The model terms will be study arm and the minimisation factors used for randomisation. The odds of a patient having a better outcome if allocated to the experimental arm will be estimated along with the associated 95% confidence interval. A Forest plot illustrating treatment effect odds ratios by minimisation factor categories will also be provided. . A test for interaction will be conducted to assess whether the effect of treatment arm depends on the other clinical factors used in the minimisation algorithm.

It will not be possible to distinguish between 0 and 1 on the WHO COVID 10-point ordinal severity scale so these will be combined in analyses.

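### The unadjusted Mann-Whitney test of toxicity grades is valid but loses power where minimisation factors predict grade, most plausibly for laboratory toxicities

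*Protocol*

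**What the plan says.** Protocol section 7.1.5 takes each patient's worst toxicity grade during active treatment, including adverse events of special interest, and says that these grades "will be compared between the study arms using the Mann-Whitney U test". It adds "P-values will be interpreted in the context of the multiple tests performed" and "This analysis will be restricted to events that occur in more than 10% of patients in either arm". No hypothesis, alpha or power is set for safety.

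On allocation, section 3.4 says "A minimisation algorithm incorporating a random component will be used to allocate patients to either experimental or control arm". The factors are site, age, hypertension or obesity, symptom duration, sex and baseline WHO level (2 or 3; 4). For the primary endpoint, section 7.1.2 says "The model terms will be study arm and the minimisation factors used for randomisation". Sections 7.1.3 and 7.1.4 carry the same terms into the logistic and Fine and Gray models. The viral load analysis in 7.1.4 uses the baseline value as a covariate.

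On adverse event recording, section 6.1.2.2 says "All AEs must be reported from the start of treatment and followed until" one of several end conditions is met. One of these is "If present at pre-treatment, until the AE returns to the level observed at that time".

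**The concern.** Minimisation makes the arms more alike on its factors than simple randomisation would. A test that ignores those factors still uses a variance that includes the spread between their levels. If the factors predict the outcome, that variance is too large, the true error rate falls below the nominal level, and power is lost. In a safety comparison this means that a real excess of toxicity is less likely to stand out.

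The protocol itself links one factor to laboratory grades:
- WHO level 4 is hospitalised without oxygen; levels 2 and 3 are ambulatory (Appendix 1).
- Inpatients have routine bloods on days 1, 3 and 8 (inpatient Schedule of Events; section 4.2.1 also lists day 11).
- Outpatients have none scheduled between screening and day 15 (outpatient Schedule of Events, section 4.2.2). Even with the 48-hour window, day 15 bloods fall no earlier than day 13, and treatment ends on day 10.

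So a laboratory grade during active treatment can be seen on schedule mainly in patients who enter at level 4. Many of the common reactions listed in section 5.7.2 are laboratory findings (uric acid, ALT and AST, white cells, neutrophils, triglycerides). ALT or AST above 3 x ULN is the event of special interest in section 5.8.

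A separate matter is the screening value. Table 2 includes ALT, AST and uric acid, and these bloods are taken at screening in both schedules. Section 3.2 admits a patient with ALT or AST between 3 and 5 x ULN if bilirubin is not above 2 x ULN. Such a patient already exceeds the special-interest threshold before any drug effect, and the planned test does not use that information.

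**Working it through.** **Inputs from the protocol.** 302 patients, 151 per arm, in an "open-label randomised (1:1) phase II/III study"; two-sided 5% level for the primary endpoint; events tested if above 10% in either arm, that is at least 16 of 151. The protocol states no safety figure to reproduce. The 302 itself does reproduce: the proportional-odds formula gives 289 for a fixed design, and 302 patients with the two interim looks give 90.2% power.

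**Step 1: general size of the effect.** If minimisation balances the factors and they explain a share R² of the rank variance, the unadjusted statistic has variance of about 1 - R². Its true two-sided size is 2[1 - Φ(1.96/√(1 - R²))]. The protocol gives no R², so a range is shown.

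| R² | Size of unadjusted test | Power where an adjusted test has 80% |
|---|---|---|
| 0 | 5.0% | 80.0% |
| 0.05 | 4.4% | 78.5% |
| 0.10 | 3.9% | 76.9% |
| 0.20 | 2.8% | 72.9% |
| 0.30 | 1.9% | 67.7% |

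A simulation of 302 patients minimised on six factors (biased coin 80% and five sites, both assumed; 2,500 runs) agrees. With no association, size was 4.7-5.0% and power matched an adjusted test (66.5% v 66.9%; 88.1% v 88.1%). With weak association the loss was 1-2 points, with moderate 5-7, and with strong 9-15.

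**Step 2: laboratory grades seen only in inpatients.** Let f be the inpatient share and p the event rate among inpatients, equal in both arms. Treating the grade as event or no event, total variance is fp(1 - fp) and variance within WHO level is fp(1 - p). So 1 - R² = (1 - p)/(1 - fp).

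| f | p | Overall rate fp | 1 - R² | Size |
|---|---|---|---|---|
| 0.3 | 0.4 | 12% | 0.6/0.88 = 0.682 | 1.8% |
| 0.5 | 0.4 | 20% | 0.6/0.80 = 0.750 | 2.4% |
| 0.7 | 0.4 | 28% | 0.6/0.72 = 0.833 | 3.2% |
| 0.7 | 0.2 | 14% | 0.8/0.86 = 0.930 | 4.2% |

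All four rows pass the 10% rule. At p = 0.2 with f = 0.3 the overall rate is 6%, so the event would not normally be tested.

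**Step 3: power.** Simulation with grades 0-3, WHO level balanced between arms, and inpatient event rates of 40% v 60% (assumed; 5,000 runs each):

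| Inpatient share | Size, unadjusted | Power, unadjusted | Power, stratified by WHO level | Loss |
|---|---|---|---|---|
| 30% | 1.5% | 25% | 43% | 18 points |
| 50% | 2.7% | 52% | 64% | 12 points |
| 70% | 3.3% | 73% | 78% | 5 points |

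The stratified test kept its size at 4.4-5.2%. A second set of runs over the same shares gave an unadjusted size of 1.3-4.3% and a loss of 2-19 points.

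**The case against.** The strongest reply is that nothing here is an error. The test is valid, the protocol makes no power claim for safety, the p-values are read descriptively, and an unadjusted safety comparison is a usual choice. Serious adverse events are all tabulated, ALT or AST above 3 x ULN is reported within 24 hours, and an independent committee reviews accruing data. The analysis plan, which is not at hand, may add a sensitivity model. All of this stands. It keeps the point to an improvement in efficiency; it does not justify giving up power when the test named in the protocol can be replaced at almost no cost.

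A reader might infer more than the documents support:
- **That the test is conservative for every event.** It is so only where the factors predict grade. For clinical events such as nausea or headache the protocol gives no such link, and the loss may be nil.
- **That ignoring baseline makes the test conservative.** A baseline value that is not a minimisation factor costs power if left out. It does not change the size.
- **That a baseline grade exists for every event.** The pre-treatment level in section 6.1.2.2 is a rule for ending follow-up. Events between consent and randomisation need not enter the CRF if unrelated to a screening procedure, so only laboratory tests have a reliable baseline.
- **That a large gain from baseline ALT applies to all 302 patients.** Outpatients have no scheduled ALT during treatment, so no such gain can be claimed for the whole trial.
- **That all six factors belong in every model.** Apart from site they need 7 parameters (age 2, hypertension or obesity 1, symptom duration 2, sex 1, WHO level 1). An event may qualify with 16 patients in one arm. Section 7.1.4 itself makes the adjusted model for outpatient viral clearance conditional on sufficient numbers.

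**Conclusion.** The point holds in a limited form. The Mann-Whitney test in section 7.1.5 does not inflate the error rate. It loses power where the minimisation factors predict grade, and the blood schedule makes that likely for laboratory toxicities through baseline WHO level. If laboratory grades are detected only in inpatients, the true error rate is about 1-4% instead of 5%, and the power loss is about 2-19 points for inpatient shares of 30-70%.

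These figures rest on assumed inpatient shares and event rates, on good balance of WHO level between arms, and on no outpatient bloods during treatment. Unscheduled bloods, later admission of outpatients or early discharge of inpatients would weaken the link and shrink the loss. This is a worthwhile improvement to a valid analysis. It gives no ground for saying that the planned safety comparison is wrong or that harm will be missed.

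**What to change.** In section 7.1.5:
1. Replace the plain Mann-Whitney test, for every qualifying event, with one pre-stated van Elteren test stratified by baseline WHO level (2 or 3 v 4). Using the same test throughout avoids choosing a method after the event counts are known.
2. For laboratory toxicities (ALT, AST, uric acid, blood counts), also report a proportional-odds model with arm, baseline WHO level and the screening value, giving the odds ratio and 95% confidence interval.
3. Do not add a pre-treatment grade as a covariate for non-laboratory events, and do not require all six factors for every event.

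The cost is a few lines of text and little programming, since section 7.1.2 already uses a proportional-odds model. Baseline WHO level and the screening bloods are already collected. Where WHO level does not predict grade, two large strata balanced between arms cost practically nothing.
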